### Procedure and instruments

The project will be structured in three visits (Fig. 1, Flow chart).

**Fig. 1 Fig1:**
[figure not shown]
Flow chart CG: Control group; IG: Intervention group; BDR: Bronchodilator responsiveness

At the first visit, all of the participants will be seen by the out-patient pneumology unit for classification of their asthma, renewal of their inhalers, and preparation of orders for complementary tests. Following this, the control group will receive instructions provided by a nurse specialized in asthma concerning the illness, the treatment to follow, signs to watch out for, plan of action, and a review of the triggers of the illness. Meanwhile, the patients from the intervention group, in addition to this instruction, will also be included in the database of the ESTOI application and will be provided access to the patient homepage, where they may find all the information needed for the management of their asthma. Both groups will be provided with a Peak Flow device and will receive instruction on how to use it and record the results in a diary.

At the conclusion of the first visit, all of the participants will be given an appointment for a second visit as well as a contact phone number to resolve any questions that may arise.

At the conclusion of the third visit, the intervention group will complete a questionnaire to determine their satisfaction with the app that they used.

All of the relevant data from the study will be collected in the case report form of each patient for subsequent analysis. The case report forms will be housed in the medical center in a locked room to which only the research team will have access.

At each of the three visits in the study, the nurse specialized in asthma will be responsible for compiling the study questionnaires (ACT, TAI, AQLQ, and HADS) of all the patients, reviewing the records of withdrawal from medication, carrying out a FeNO test, doing spirometry with bronchodilator, ordering bloodwork, and making on-site PEF measurement. All of the data will be duly recorded in the case report forms.

A nurse trained in telemedicine will be in charge of the management and monitoring of the patients using the application. The nurse will also be responsible for making appointments, reviewing the clinical records of all the patients included in the study, and managing the case report and informed consent forms. The nurse specialized in asthma will be responsible for administering the questionnaires, collecting the case report form data, and the carrying out of the blood tests and pulmonary function testing.

### ESTOI application for the management of asthmatic patients

The mobile application ESTOI, created and managed by the research team of this study, is designed to provide, in a personalized manner, all of the tools normally used in a hospital for the management and control of asthma. ESTOI has a number of components that may be managed and modified by the researchers in response to the needs of each patient. It is available for both Android and IOS devices.

In the first component, ‘CONTROL OF SYMPTOMS’, the participants respond to questions about their health that are designed in a personalized manner in order to learn of their current asthma state. Each month the ACT, TAI, number of exacerbations, and weight will be recorded, as well as, depending on the case, data on the control of symptoms of rhinitis, nasal polyposis, RGE, allergies, and smoking habit, if any. Depending on the results obtained from the questionnaire, the patient will be given recommendations or alerts in accordance with the seriousness of their situation, and the application will automatically alert the medical team when a serious worsening in control of the illness is detected, so as to allow for management of the situation and avoidance of future risk.

In the second component, ‘HEALTH RECOMMENDATIONS’, all of the information that the patient needs to manage the pathology is shown, including how to control it and what to do in the event of a worsening of the symptoms. The recommendations that appear in this component will depend on the patient’s state and comorbidities; only information appropriate to the current state of the patient will be available to him or her.

In the third component, ‘YOUR TREATMENT’, appears up-to-date, personalized information concerning current medication used by the patient to treat asthma, the dosage and times to take the medication, and, in the case of inhalers and biological therapy, a video explaining how they are to be administered. This component also includes the plan of action, showing the medication to be taken by the patient in the event of a worsening of the asthma, as well as in the event of an emergency. Both the treatment and the plan of action will be reviewed and modified, if necessary, at each patient visit to pneumology.

In the fourth component, ‘PEAK FLOW’, the patient can record the measurements made using the Peak Flow Meter at home. The peak flow is calculated automatically in order to reveal whether there have been significant changes in the values for pulmonary function, so that treatment can be modified and adjusted to current needs without the need for the patient to visit a medical center.

The fifth component, ‘NUTRITIONAL PLAN’, provides a guide to daily foods so that the individual may adapt the tools and advice to his or her needs.

The sixth and final component, ‘MESSAGING’, provides for two-way communication between the participants and the members of the specialized asthma medical team, allowing for additional information to be provided and for questions to be answered.

### Analysis of the data

The continuous variables are expressed as mean and standard deviation in case of normal distribution, and median and interquartile range in case of non-normal distribution. The qualitative variables are to be defined as frequencies and percentages. For comparison of the continuous variables the variance analysis method (ANOVA) or the Kruskal-Wallis test will be used. For analysis of the main assessment, the Chi-squared test will be used. Stepwise logistic regression models will be used to select the subgroup with parameters significantly associated with poor control of asthma. A priori, the factors to be included in the analysis are age, number of years suffering asthma, education level, IMC, smoking, environmental exposures, pre-BD FEV1, post-BD FEV1, FeNO, blood eosinophils, general and specific blood IgE, ACT, TAI, HAD, AQLQ, number of exacerbations, and control of comorbidities that affect asthma (GERD, rhinitis, nasal polyposis, overweight/obesity, and smoking). Statistical significance will be set at *p* < 0.05.

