### Calculation of the sample

In order to calculate the sample size, a screening of 60 patients seen in the pneumology unit of the center was made with the ACT questionnaire, in order to learn the degree of current control of the asthma of those patients.

With a CI of 95% and a standard deviation of 4.95, the average ACT score of the patients seen in our center was 18.43 ± 1.25. The calculation of the sample size was based upon the established aims. We used the Granmo 7.12 program for two independent averages, accepting an alpha risk of 0.05 and a beta risk of 0.2 in bilateral contrast. Some 54 subjects were determined to be needed for each group in order to detect a difference equal to or greater than 3 units in the ACT questionnaire [16, 17]. We assumed a common standard deviation of 4.95 (obtained by screening in our center) and calculated a rate of loss in follow-up of 20%.

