### Variables

The main variable of the study will be ACT. Evaluation will be made of the participants in both groups, at the beginning of follow-up, at 6 months, and at 12 months. The results obtained will be compared. In addition, sociodemographic variables will be collected, such as age, sex, education level, and experience in the use of mobile applications. The study variables are detailed in Table 2.

**Table 2 Tab2:** Study variables

Variable	Description	When will it be used?
**Asthma Control Test (ACT)**	ACT is a 5-item questionnaire that assesses the level of control of asthma symptoms during the previous 4 weeks [19].	CG at each visit (v1, v2, v3) IG once a month (using the ESTOI app) and at each visit of the study (V1, V2, V3)
**Test of the Adherence to Inhalers (TAI)**	TAI is a 12-item questionnaire that assesses adherence to inhalers for patients with Asthma or COPD [20].	CG at each visit (v1, v2, v3) IG once a month (using the ESTOI app) and at each visit of the study (V1, V2, V3)
**Asthma Quality of Life Questionnaire (AQLQ)**	AQLQ is a 32-item questionnaire that assesses the quality of life of patients with asthma. Covers 4 dimensions (breathlessness, mood, social limitation and worrying) [21].	Both groups (IG and CG) at each visit (V1, V2, V3)
**The Hospital Anxiety and Depression Scale (HADS)**	HADS is a questionnaire for detecting affective disorders in hospital settings with outpatients. Is frequently used to evaluate populations with chronic diseases [22].	Both groups (IG and CG) at each visit (V1, V2, V3)
**Blood eosinophil count**	Eosinophils are actively involved in diseases caused by parasites and in allergic reactions. In the case of asthma, having eosinophils in range is usually an indicator of good control [4].	Both groups (IG and CG) at V1 and V3
**Immunoglobulin E (IgE)**	IgE is an antibody involved in airway inflammation and allergic reactions. It plays an essential role in modulating severity as a direct association between IgE concentrations and increased disease severity, bronchial hyperresponsiveness and reduced lung performance [4].	Both groups (IG and CG) at V1 and V3

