### Limitations

As this is a single-center study, the results may not be representative of the general population, which limits our ability to extrapolate the findings to different clinical settings. In an attempt to offset this limitation, and to ensure that the results are as extrapolable as possible, we will use the standards laid out in the Spanish Guide for the Management of Asthma (GEMA) [1]. To learn the degree of control of the illness we will take into account the number of exacerbations suffered in the past year, the asthma symptoms measured with ACT [19], and pulmonary function, using as measuring tools the PEF and the FEV1. With the aim of determining the degree of adherence to treatment we will use the TAI questionnaire and will review the electronic history of withdrawal from prescribed medication [1, 20]. For quality of life, we will make recourse to the AQLQ and the HAD [21, 22].

Given that the proposed intervention has simple masking, the research team and the clinical staff will be aware at all times which patients belong to which group, and this could influence the behavior of the staff as well as the manner in which the results are evaluated. As a result of randomization, it may be difficult to ensure that the groups are completely comparable in all areas.

Another limitation to bear in mind is the time stipulated for follow-up, which is limited and which may impede assessment of the effectiveness of the telemedicine program over the long-term in the control of asthma.

Finally, the participants may not comply completely with the recommendations made to them, or they may abandon the study prematurely, which would cause skewing in the results and render assessment of the real effectiveness of the telemedicine program in the control of asthma difficult. In addition, assessment of the control of asthma often involves subjective measurement of symptoms and quality of life, which could be influenced by the individual perception of the participants.

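### No between-arm test named in the plan uses the V1 baseline, so the ACT comparison gives up precision that the collected data would supply

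*Protocol article*

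**What the plan says.** Under Variables, the Protocol article states "The main variable of the study will be ACT" and sets its timing: "Evaluation will be made of the participants in both groups, at the beginning of follow-up, at 6 months, and at 12 months". Table 2 also schedules TAI, AQLQ, HADS, PEF, FVC, FEV1 and FeNO at V1, V2 and V3 in both groups, and blood eosinophils and IgE at V1 and V3. Every continuous outcome therefore has its own baseline value.

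Analysis of the data names two kinds of comparison. For continuous variables: "For comparison of the continuous variables the variance analysis method (ANOVA) or the Kruskal-Wallis test will be used". For the primary question: "For analysis of the main assessment, the Chi-squared test will be used". Neither sentence mentions a baseline value.

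The only multivariable model has another purpose: "Stepwise logistic regression models will be used to select the subgroup with parameters significantly associated with poor control of asthma". ACT is among its candidate factors, but treatment arm is not, so it is not the comparison of the two groups.

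Calculation of the sample treats the trial as a comparison of two independent means with a common SD of 4.95, "accepting an alpha risk of 0.05 and a beta risk of 0.2 in bilateral contrast", and 20% loss: "Some 54 subjects were determined to be needed for each group in order to detect a difference equal to or greater than 3 units". Limitations concedes that after randomization "it may be difficult to ensure that the groups are completely comparable in all areas".

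**The concern.** The baseline value of an outcome usually predicts its follow-up value. A comparison that leaves it out carries explainable variation in its standard error. It also leaves any chance difference between the arms at V1 inside the estimated effect. In a trial expecting about 43 evaluable patients per arm, both effects can matter. The article recognises possible non-comparability of the groups, but neither the allocation it describes (a randomization grid, with no stratification by ACT mentioned) nor the tests it names address this for ACT.

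The named tests also sit awkwardly with the 3-unit target. Neither Chi-squared nor Kruskal-Wallis yields a mean difference in ACT units with a confidence interval to set against it.

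**Working it through.** **Inputs from Calculation of the sample.** Difference 3 ACT units; SD 4.95; two-sided alpha 0.05; power 80%; loss 20%; 54 per group.

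**Assumptions not in the article.** The V1-to-12-month ACT correlation r is not given and is taken as 0.3, 0.5 and 0.7. The SD of 4.95 from the centre's screening sample is used at both V1 and follow-up. Twelve months, the end of follow-up, is taken as the time point.

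**1. The plan's own figure.** n per arm = 2 × [4.95 × (1.960 + 0.842) / 3]² = 42.7, so 43. Allowing for loss, 43 / 0.8 = 53.75, so 54. The stated size reproduces. Power with 43 evaluable per arm, unadjusted, is 79.3% by the noncentral t distribution and 80.2% by the normal approximation.

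**2. Effect of adjusting for V1 ACT.** Residual SD = 4.95 × √(1 − r²). Power is for 3 units with 43 per arm, by noncentral t. The detectable difference at 80% power is (1.960 + 0.842) × residual SD × √(2/43), by the normal approximation.

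| r | Residual SD | Power | Detectable difference (units) |
|---|---|---|---|
| unadjusted | 4.95 | 79.3% | 2.99 |
| 0.3 | 4.72 | 82.9% | 2.85 |
| 0.5 | 4.29 | 89.4% | 2.59 |
| 0.7 | 3.54 | 97.3% | 2.14 |

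The reference row is an unadjusted comparison of ACT means, as in the sample size. It is not the Chi-squared test.

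**3. Chance baseline difference in ACT.** SE = 4.95 × √(2/n).

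- 43 per arm: SE 1.07; 95% range ±1.96 × 1.07 = ±2.1 units; the gap exceeds 1 unit in about 35% of randomizations.
- 54 per arm: SE 0.95; 95% range ±1.9 units; the gap exceeds 1 unit in about 29%.

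**4. How much of that reaches the result.** With equal SDs at V1 and follow-up, a baseline gap d shifts the unadjusted follow-up difference by about r × d. At the edge of the 95% range with 43 per arm (2.09 units):

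- r = 0.3: 0.63 units, 21% of the 3-unit target
- r = 0.5: 1.05 units, 35%
- r = 0.7: 1.46 units, 49%

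**5. Would a change-score ANOVA do as well?** The SD of change is 4.95 × √(2(1 − r)). With 43 per arm, by the normal approximation, power is 66%, 80% and 95% at r = 0.3, 0.5 and 0.7. Covariate adjustment on the same approximation gives 84%, 90% and 98%. The change score is less powerful at each value, and at r = 0.3 it falls below the unadjusted 80%.

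**The case against.** Four arguments stand against the point.

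**The unadjusted comparison is valid.** Under randomization it is unbiased and keeps its type I error, and its standard error already allows for chance imbalance. The trial was sized on the full SD and meets its stated power without adjustment. This stands in full. A reader might infer that the plan is underpowered or its inference invalid; the documents do not support that.

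**A baseline gap does not pass whole into the result.** A reader might set ±1.9 or ±2.1 units directly against the 3-unit target. That is the range of the baseline difference itself, and only about r times it reaches the follow-up comparison. The admission in Limitations is a general caution and does not show that imbalance will occur.

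**The Chi-squared sentence governs the main assessment.** A reader might take the rise from 79% to 89% as the gain over the written primary analysis. It is the gain over an unadjusted comparison of means, the analysis on which the sample size rests. This limits the claim. It also means that amending only the ANOVA sentence would leave the plan inconsistent on ACT.

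**The article is condensed.** It names a family of tests and does not say whether ANOVA applies to follow-up values, to change or to repeated measures; a fuller plan might. This stands in part. The article does commit to named tests, with no covariate stated and with Kruskal-Wallis as the alternative, and a change score would not recover the full gain (step 5).

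The correlation is also unknown. Participants are first-time clinic patients, and both arms receive inhaler renewal and nurse instruction at V1, so a weak correlation is plausible. At r = 0.3 the gain is modest.

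**Conclusion.** The point holds as an avoidable loss of precision. No between-arm test named in the article is described with a baseline term, although the V1 values will be in hand. Relative to an unadjusted comparison of means, adjustment adds about 4, 10 or 18 percentage points of power at r = 0.3, 0.5 or 0.7. It also removes a chance shift that, at the edge of the 95% range, would be about 0.6 to 1.5 ACT units.

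These sizes rest on an assumed correlation, a V1 SD of 4.95 and 43 evaluable patients per arm. That adjustment helps for any non-zero correlation does not depend on the particular value, apart from the negligible cost of one extra model term.

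**What to change.** Replace both sentences in Analysis of the data as far as they govern the between-arm comparison:

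- **Primary.** Analyse 12-month ACT by a linear model with arm and V1 ACT. Report the adjusted mean difference with its 95% CI and read it against the 3-unit target. Keep any Chi-squared comparison of controlled asthma as a secondary analysis.
- **Continuous secondaries.** Use the same model, each outcome with its own V1 value. A log transform for skewed biomarkers (FeNO, IgE, eosinophils) is optional.
- **Stepwise logistic model.** It may stay as an exploratory search for factors linked to poor control, stated to be separate from the treatment comparison.

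The cost is a change of analysis wording, best made before outcome data by arm are seen. It needs no extra patients, visits or measurements, and the sample size of 54 per arm can stay.

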**Methodology:**

Randomized clinical trial with 52 weeks’ follow-up of patients with asthma seen in a specialized hospital for their treatment in Spain. Some 108 included patients will be divided into two groups. The intervention group will undergo more exhaustive follow-up than normal, including access to the ESTOI application, which will have various categories of attention: control of symptoms, health recommendations, current treatment and personalized action plan, PEF record, nutritional plan, and chat access with a medical team. The asthma control questionnaire ACT is the main assessment variable. Other variables to be studied include an adherence test for the use of inhalers (TAI), the number of exacerbations, maximum exhalation flow, exhaled nitric oxide test, hospital anxiety and depression scale, asthma quality-of-life questionnaire, forced spirometry parameters (FVC, FEV1, and PBD), and analytic parameters (eosinophilia and IGE). The data will be collected during outpatient visits.

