**Exacerbation**	In asthma an exacerbation is considered a worsening of asthma symptoms that requires medical intervention and has at least 1 of the following 3 elements listed below for at least 2 consecutive days: Worsening of asthma signs/symptoms (dyspnea, wheezing, nocturnal awakenings, or chest tightness), increased use of rescue medication or deterioration of lung function [1].	CG at each visit (v1, v2, v3) IG once a month (using the ESTOI app) and at each visit of the study (V1, V2, V3)
**Peak Expiratory Flow (PEF)**	PEF is the highest airflow achieved in a forced expiration after an also forced inspiration, measured using a Peak Flow Meter. It is used as a predictor of airway obstruction [23].	Both groups (IG and CG) once a week (using the ESTOI app in case of IG) and at each visit of the study (V1, V2, V3)
**Forced vital capacity (FVC)**	FVC is the total volume of air that can be exhaled during a maximum effort of forced expiration without a time limit [24].	Both groups (IG and CG) at each visit (V1, V2, V3)
**Forced expiratory volume in one second (FEV1)**	FEV1 is the volume of air exhaled in the first second under force after a maximal inhalation [24].	Both groups (IG and CG) at each visit (V1, V2, V3)
**Bronchodilator Responsiveness (BDR)**	BDR determines the degree of airflow improvement after the administration of a Beta-2 adrenergic agonist. The test is considered positive when there is an increase from baseline values of FEV1 by at least 12% and 200 mL [24].	Both groups (IG and CG) at each visit (V1, V2, V3)
**Fractional exhaled nitric oxide (FeNO)**	FeNO is a useful and noninvasive biomarker for eosinophilic airway inflammation, particularly in asthma [25].	Both groups (IG and CG) at each visit (V1, V2, V3)

*CG* Control group, *IG* Intervention group

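### By elimination, the number of exacerbations would be compared by ANOVA or Kruskal-Wallis, which ignore follow-up time; the main cost is modest power, and bias only under further conditions

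*Protocol article*

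**What the plan says.** The data analysis section recognises two classes of variable, continuous and qualitative. For the first it states: "For comparison of the continuous variables the variance analysis method (ANOVA) or the Kruskal-Wallis test will be used". For the second: "The qualitative variables are to be defined as frequencies and percentages". Two further methods are named: "For analysis of the main assessment, the Chi-squared test will be used", and stepwise logistic regression for factors linked to poor control. The number of exacerbations appears in that section only as a candidate factor for the logistic model.

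The abstract lists exacerbations among the secondary variables: "Other variables to be studied include an adherence test for the use of inhalers (TAI), the number of exacerbations". Table 2 gives the recording schedule as "CG at each visit (v1, v2, v3) IG once a month (using the ESTOI app", with study visits added for the intervention group. The variables section places assessments at baseline, 6 and 12 months. The limitations section, on judging disease control, refers to "the number of exacerbations suffered in the past year".

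The sample size section "calculated a rate of loss in follow-up of 20" per cent, with no split by arm. Table 1 lists loss to follow-up as a withdrawal criterion.

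**The concern.** A count observed over unequal time is not a continuous measurement. ANOVA and Kruskal-Wallis give a patient followed for half the year the same standing as one followed for the whole year. With 20% loss planned, the stated rule leaves two routes: compare raw counts over unequal time, or drop everyone with partial follow-up.

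The first route makes an arm with more early loss look better than it is. The second discards observed events. On either route, a rank test on skewed counts with many zeros is inefficient and gives no rate ratio. At stake are the precision and interpretability of one secondary comparison in a trial of 54 patients per arm.

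**Working it through.** **Plan's own figure.** ACT difference 3, SD 4.95, two-sided alpha 0.05, power 0.80:

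n = 2 × (1.960 + 0.842)² × 4.95² / 3² = 2 × 7.849 × 24.50 / 9 = 42.7, so 43 per arm. Then 43 / (1 − 0.20) = 53.75, so 54 per arm, as stated. Exacerbations play no part in this.

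**Inputs for the check.** From the article: 54 per arm, 52 weeks, 20% loss, visits at 0, 6 and 12 months. Assumed, because the article gives no figures: annual rate, dispersion, rate ratio, loss by arm, drop-out uniform over the year and unrelated to exacerbations. Counts were simulated as over-dispersed (gamma-Poisson).

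**Power, 20% loss in both arms, true rate ratio 0.5** (1,000 simulated trials per row, power in %):

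| Rate, dispersion | Rate model with offset | ANOVA, all | Kruskal-Wallis, all | ANOVA, completers | Kruskal-Wallis, completers |
|---|---|---|---|---|---|
| 1.0, 1.0 | 58.1 | 54.5 | 49.2 | 50.0 | 45.8 |
| 2.0, 0.5 | 87.6 | 85.8 | 79.3 | 81.6 | 73.6 |
| 2.0, 1.0 | 76.0 | 71.1 | 60.8 | 66.7 | 55.3 |

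- Kruskal-Wallis on all counts loses 8.9, 8.3 and 15.2 points; on completers 12.3, 14.0 and 20.7.
- ANOVA on all counts loses 3.6, 1.8 and 4.9 points; on completers 8.1, 6.0 and 9.3.
- Over a wider grid (rates 0.5, 1 and 2), the losses on all counts were 3 to 15 points for Kruskal-Wallis and −1 to +5 for ANOVA.
- At rates of 1.0-1.5 with a negative binomial comparator, the losses on all counts were about 10-13 points for Kruskal-Wallis and 2-5 for ANOVA.

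With no drop-out at all (rate 1, dispersion 1), Kruskal-Wallis still had 51% against 62% for negative binomial, a gap of 11 points. At that rate and dispersion, much of the shortfall is therefore the rank test and not follow-up time. This fits the exposure arithmetic: with 20% uniform loss, mean observed time is 1 − 0.20/2 = 0.90 years, so little time is lost.

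**Bias, no true effect, unadjusted counts.**

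If events are counted up to the moment of drop-out, mean observed time is 1 − d/2 for loss d:

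- 10% v 30%: 0.85 / 0.95 = 0.89 (simulated 0.88-0.92)
- 0% v 40%: 0.80 / 1.00 = 0.80 (simulated 0.80-0.82)

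If counts come only from visits at 6 and 12 months, half of those lost have no post-baseline count and half have a 6-month count. The mean exposure among patients with data is (1 − 0.75d) / (1 − 0.5d):

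- d = 0.10: 0.925 / 0.95 = 0.974; d = 0.30: 0.775 / 0.85 = 0.912; ratio 0.94 (simulated 0.93-0.94)
- d = 0.40: 0.70 / 0.80 = 0.875; ratio 0.88 (simulated 0.85-0.88)

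Type I error at 10% v 30% was 6-10% with continuous counting. With visit-based counts it was 4.4% (Kruskal-Wallis) and 6.2% (ANOVA) in 500 trials; the Monte Carlo standard error is √(0.05 × 0.95 / 500) = 1.0 point, so there is no clear inflation. At 0% v 40% it was 10-25% with continuous counting and about 9-10% visit-based. Completers-only tests stayed at 3.6-6.1%, and the offset model at 3.5-7.0% with ratios of about 0.98-1.02.

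With a true ratio of 0.50, the continuous-count ratio became 0.44-0.45 (control 10%, intervention 30%) or 0.55-0.57 (30%, 10%). The direction depends on which arm loses more.

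**The case against.** The article never assigns exacerbations to ANOVA or Kruskal-Wallis; that is reached by elimination. It is a condensed article, its statistical analysis plan is not shown, and the handling of partial follow-up for a secondary variable is often left to that plan. Control-arm counts come only from visits, so a control patient lost at month 2 contributes no post-baseline count. If exacerbations are taken as a 12-month recall at the last visit, everyone who attends has equal exposure. ANOVA, the first test named, loses little.

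Most of this stands and sets the size of the point. It does not remove the point. The article does more than stay silent: it states a rule for numeric comparisons, that rule suits this outcome badly, and no other named method fits. The 12-month recall equalises exposure only by dropping those who miss the last visit, which is the completers-only route with its power cost.

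A reader might infer that the comparison will be biased, or that false positives will reach 19-25%. The documents do not support this. They give no loss by arm and do not say that partial counts will be used unadjusted; the large figures come from an extreme 0% v 40% split with continuous counting. A reader might also attribute the whole power loss to ignored follow-up time; the zero-drop-out result argues against that.

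**Conclusion.** The point holds in limited form. ANOVA or Kruskal-Wallis is the only stated between-arm rule that fits a numeric outcome, so by elimination it covers "the number of exacerbations", and it takes no account of follow-up time.

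The main consequence is lost power: roughly 10 points for Kruskal-Wallis, the likely branch for skewed counts, more on completers, and about 2-5 for ANOVA on all counts. Bias is conditional on unequal loss together with unadjusted partial counts, and is small at 10% v 30%. A completers-only analysis avoids it when loss is unrelated to outcome.

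These sizes rest on assumed rates, dispersion, rate ratio and drop-out pattern. The offset model likewise assumes that loss is unrelated to exacerbation risk. The outcome is secondary; the sample size and the ACT analysis do not depend on it.

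**What to change.** Add a sentence to the data analysis section: on-study exacerbations, in all randomised patients with post-baseline data, will be analysed by negative binomial (or over-dispersed Poisson) regression with study arm as the effect and log observed time as offset, and reported as a rate ratio with 95% CI. If the prior-year count is recorded at baseline, include it as a covariate.

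State also that counts come from the same visit-based source in both arms. The intervention arm is additionally recorded monthly through the app, and an offset does not correct for unequal recording.

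The cost is slightly more programming and a date of last contact on the case report form. No patients or procedures are added, and 54 per arm stays as it is.

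### The trial is sized on a 3-unit difference in mean ACT, but the analysis section does not commit to estimating that difference

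*Protocol article*

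**What the plan says.** Under Variables, the protocol article states: "The main variable of the study will be ACT". It is assessed in both groups at the start, 6 months and 12 months.

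Under Calculation of the sample, the trial is sized for two independent means, "accepting an alpha risk of 0.05 and a beta risk of 0.2 in bilateral contrast", "in order to detect a difference equal to or greater than 3 units in the ACT questionnaire". The SD is 4.95, taken from 60 screened patients, and 20% loss is allowed for. The result: "Some 54 subjects were determined to be needed for each group".

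Under Analysis of the data, three statements bear on how ACT would be handled:

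- Continuous variables are summarised as "mean and standard deviation in case of normal distribution, and median and interquartile range in case of non-normal distribution".
- "For comparison of the continuous variables the variance analysis method (ANOVA) or the Kruskal-Wallis test will be used". No criterion for choosing between the two is given.
- The sentence after that assigns the main assessment to a chi-squared test.

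No sentence in the section names a between-arm difference in mean ACT as a quantity to be estimated. Under Limitations, the article says that the research team and clinical staff know allocation throughout and that this could affect how results are evaluated.

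**The concern.** The design question is how many ACT units the app adds on average. Each route through the analysis section can miss it. A chi-squared test compares proportions. A rank test with medians compares the ordering of scores. Only the ANOVA branch with means addresses the design quantity, and nothing in the text ensures that this branch is taken.

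Correcting the chi-squared line alone would not settle the matter. It would move ACT onto the ANOVA or Kruskal-Wallis sentence, where the choice is still open. That sentence already covers AQLQ, HADS and TAI when they are treated as scores, and AQLQ and TAI carry the quality-of-life and adherence parts of the stated aim.

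At stake is a result that could be significant at p < 0.05 and still not say whether the 3-unit target was met, with the method chosen by people who know the arms.

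**Working it through.** **1. The plan's own figure.** Inputs from Calculation of the sample: difference 3, SD 4.95, two-sided alpha 0.05, power 0.80, loss 20%.

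- n per group = 2 × (1.960 + 0.842)² × 4.95² / 3² = 42.7, rounded up to 43.
- With loss: 43 / 0.80 = 53.75, rounded up to 54. This matches the plan.
- Screening interval: 1.96 × 4.95 / √60 = 1.25. This matches "the average ACT score of the patients seen in our center was 18.43 ± 1.25".

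The design is therefore a comparison of means. With 43 evaluable per group, the standard error of the mean difference is 4.95 × √(2/43) = 1.07. The 95% confidence interval would be about ± 1.96 × 1.07 = ± 2.1 units. That is the information lost if no mean difference is reported.

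**2. How often would ACT be judged non-normal?** The documents give no normality test, score range or distribution, so all three are assumed here. Control mean 18.43, intervention mean 21.43 before any ceiling, SD about 4.95 (3.9 in the intervention arm of the skewed shape), 43 or 54 per group, 2,000 runs each. Share of trials in which at least one arm is rejected at 5%:

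| Assumed shape | Shapiro-Wilk | Kolmogorov-Smirnov |
|---|---|---|
| Skewed, bounded 5–25 | 100% | 61–85% |
| Normal, cut off at 5 and 25 | 99.8–99.9% | 13–23% |
| Normal, rounded | 14–15% | under 1% |
| Normal | 9–10% | 0–0.1% |

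The Kolmogorov-Smirnov column uses the estimated mean and SD without correction, as is often done, and this makes the check conservative. For one control-like arm alone at 43 patients, Shapiro-Wilk rejects in about 44% to 88% of runs across the two bounded shapes.

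**3. Type I error** (bounded 5–25 score unless stated, 43 per arm, 4,000 trials). Comparison of means: 5.0–5.1%. Shapiro-Wilk first, then t-test or Kruskal-Wallis: 4.8%, and 5.0–5.6% with rounded normal data. Taking whichever p-value is smaller, which the plan does not propose: 5.6–6.2%.

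**4. Power at 43 per arm.**

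- Roughly normal scores: 79% for means, 77–78% for ranks.
- Bounded score, general upward shift of 3: 86–87% for means, 89–90% for ranks.
- Bounded score, only patients below 20 gain 5 units (mean difference about 2.6): 81–82% for means, 67% for ranks.

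**5. Effect measure.** Under the general shift, the difference in medians has an SD of about 1.4 and a 95% range of 1 to 6, against an SD of about 1.0 for the mean difference. It is too coarse to judge a 3-unit target.

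**The case against.** The case for leaving the text alone has several parts.

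- **Chi-squared, not the normality rule, governs the main assessment.** This stands. As written, the mean difference goes unestimated first because of that line. The sentence on ANOVA or Kruskal-Wallis reaches ACT only if ACT is also analysed as a score.
- **The link from normality to the test is inferred.** This also stands: the text ties normality only to the summary statistic. The inference is natural, and without it the choice has no stated basis at all.
- **A reader might infer that ACT will almost surely be ranked.** The documents do not support that. Near-certainty appears only with Shapiro-Wilk and an assumed 5–25 bound. The one sign of the team's practice points the other way, since the screening scores are reported as a mean with an SD.
- **A reader might infer error inflation or a general loss of power.** The calculations show neither. The 67% figure comes from one constructed pattern of benefit, and ranks do slightly better under a general shift.
- **ANOVA or Kruskal-Wallis is a conventional, valid choice, and a test can be reported beside an estimate.** True. The plan does not forbid reporting a mean difference.
- **A fuller protocol or analysis plan may settle this.** It may, and an article may condense. But the section does more than stay silent: it states a chi-squared test, a data-dependent summary and a choice of two tests, and these do not line up with the quantity used for sizing.

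**Conclusion.** The point holds in limited form. The trial is sized on a 3-unit difference in mean ACT, and the stated analysis does not commit to estimating it. If ACT or another questionnaire score is analysed as a score and judged non-normal, the planned output is medians and a rank p-value. That is plausible for a five-item questionnaire score, but its probability cannot be fixed from the documents.

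The cost is the effect estimate (an interval of about ± 2.1 units on the design assumptions) and a choice of method left open to an unmasked team. Nothing says who checks the distributions or when, so this is an opening for bias and not evidence of it. The 5–25 range, the cut at 20, the score shapes and the normality tests used above are assumptions. The mismatch between the sizing and analysis sections does not depend on them. It should be corrected, and doing so is simple.

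**What to change.** In Analysis of the data, together with reconciling the chi-squared line with the sample-size section:

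- State that ACT is compared between arms as a mean difference with a 95% confidence interval, whatever the observed distribution. Robust standard errors are optional.
- Say the same for the AQLQ, HADS and TAI scores.
- Keep Kruskal-Wallis as a sensitivity analysis only.

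The cost is one or two sentences. The sample size is unchanged at 43 evaluable and 54 recruited per group. The downside is slightly lower power than ranks if benefit takes the form of a general shift in a bounded score (86–87% against 89–90% above).
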